### Randomization and blinding

Patients who are scheduled to be discharged from the hospital each day will be randomly assigned to the smartwatch intervention group, the wristband group, and the control group at a ratio of 1:1:1. The randomization process is as follows: According to the predetermined number 1 for the smartwatch intervention group, number 2 for the wristband group, and number 3 for the control group, a slip of paper with numbers 1, 2, and 3 will be placed into a sealed, opaque envelope by a research assistant who is unaware of the design of the study. The number selected will determine the group to which the patient will be assigned until 61 subjects are in each group. Because participants in different groups may be in the same hospital room, all participants in the smartwatch intervention group and the wristband group will sign a confidentiality agreement stating that the study will not be disclosed to participants in the control group. Research assistants will generate the allocation sequence and enroll participants, and the researcher will assign interventions.

Because of the nature of the intervention, intervention practitioners cannot be blinded, but patients, data collectors, and statisticians will be blinded to the intervention allocation. In addition, the outcomes of this study will be objectively measured and not influenced by the unblinded intervention. Unblinding will be done after the study.

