### Recruitment

The recruitment sites for this research are the departments of neurology, West China Hospital of Sichuan University and department of neurology, Chengdu Second People's Hospital. They are all in Chengdu, Sichuan province, China. Each day from 15:00 to 17:00, the research assistants will go to the nurses’ station to collect the basic information of patients who are going to be discharged the next day and screen patients according to the inclusion and exclusion criteria. Then, the research assistants will invite the patients to the nurse station for communication and explain the purpose, significance, specific implementation process, and precautions of the project and invite patients to participate in this study. After obtaining the patient’s consent, the research assistant will record the patient’s basic information (i.e., name, sex, age, disease condition) and contact information and invite patients to join the study’s WeChat group. For the purpose of intention-to-treat analysis, if a participant drops out of the study, the research assistant will also record their basic information and the reasons for withdrawal for comparison with the enrolled participants.

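### The research assistants who enrol patients also generate the allocation sequence, which undercuts the envelope's concealment; drawing slips to 61 per arm adds predictability of an unsettled amount

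*Protocol article*

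**What the plan says.** All of this is in the Methods of the protocol article.

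**Randomization and blinding**
- Patients due for discharge "will be randomly assigned to the smartwatch intervention group, the wristband group, and the control group at a ratio of 1:1:1".
- The device: "a slip of paper with numbers 1, 2, and 3 will be placed into a sealed, opaque envelope", and this is done "by a research assistant who is unaware of the design of the study".
- The stopping rule: "The number selected will determine the group to which the patient will be assigned until 61 subjects are in each group".
- The roles: "Research assistants will generate the allocation sequence and enroll participants, and the researcher will assign interventions".

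**Recruitment**
- Each afternoon, research assistants go through the coming discharges and check eligibility.
- For eligible patients the article says that "the research assistants will invite the patients to the nurse station for communication and explain the purpose, significance, specific implementation process". They also take consent.

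The section on randomization does not say whether a drawn slip goes back, whether patients share one envelope or have one each, or who draws. It also does not say whether the assistant who fills the envelope is someone other than the assistants who generate the sequence and enrol.

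**The concern.** Concealment means that whoever decides on a patient's entry cannot know the next allocation. Here two descriptions stand side by side. In one, an uninformed assistant seals slips in an opaque envelope. In the other, the enrolling role makes the sequence. The second removes what the first is meant to provide, because an envelope hides nothing from the people who produced its contents.

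Someone who knows or can guess the next arm can hurry, delay or discourage a particular patient. The arms would then differ at baseline in ways such as motivation or fitness, which bear on the self-management and quality-of-life questionnaires among the primary outcomes. Adjustment cannot reliably remove selection on things that were not measured.

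A cap of 61 per arm also matters, because arms that fill up and close make the remaining allocations easier to foresee.

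**Working it through.** **1. The cap.** Under Sample size, 53 per group is increased by 15%: 53 × 1.15 = 60.95, rounded up to 61, and 3 × 61 = 183. The stated figures are reproduced.

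**2. The roles.** Setting the two sections side by side:

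| Task | Who, as written |
|---|---|
| Fill the envelope | a research assistant who does not know the design |
| Generate the sequence | research assistants |
| Screen, explain, obtain consent | research assistants |
| Enrol | research assistants |
| Assign the intervention | the researcher |

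Generation and enrolment fall to the same role. Anyone who holds the generated sequence can know up to all 183 allocations in advance. No simulation is needed for this part.

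**3. The slip draw alone.** Suppose the enroller has not seen the sequence but keeps count of the arms. The text permits three readings. Chance is 1/3 = 33.3%.

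*(a) Independent draws, with an arm closed once it holds 61.* In 10,000 simulated sequences of 183:
- On average 19.4 allocations come after the first arm has closed.
- On average 6.8 come after the second has closed and are therefore certain (median 6, 95% range 1 to 18).
- The stretch with two arms open is 19.4 − 6.8 = 12.6.
- All three arms are open for 183 − 19.4 = 163.6.
- Expected correct guesses from knowing only which arms are open: 163.6/3 + 12.6/2 + 6.8 = 54.5 + 6.3 + 6.8 = 67.6, and 67.6/183 = 37.0%.

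*(b) One urn with 61 slips of each number, drawn without replacement.*
- The certain allocations are the final run of one number. Given the last slip, 60 slips of its number and 122 others precede it, so the expected run is 1 + 60/(122 + 1) = 1.49. Simulation gives 1.48.
- Guessing the arm with most slips left is right 38.8% of the time (simulation).

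*(c) Three slips used up before refilling, which is a fixed block of three.*
- Every third allocation is certain: 183/3 = 61.
- The best guess is right (1/3 + 1/2 + 1)/3 = 61.1% of the time.

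| Reading | Certain in advance, of 183 | Best guess right |
|---|---|---|
| (a) independent draws, cap 61 | about 7, plus about 13 limited to two arms | 37% |
| (b) one urn, 61 per arm | about 1.5 | 39% |
| (c) three slips, then refill | 61 | 61% |

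**The case against.** The strongest reply is that the section does describe safeguards. The envelope is sealed and opaque, its filler does not know the design, and a researcher, not the enrolling assistants, assigns interventions. The filler may well be a different person from the assistants who recruit; the text does not show otherwise, and a reader should not infer that one individual does everything. That much stands. It does not remove the problem, because the section still says that research assistants generate the sequence and enrol. A separate person handing out the intervention does not hide an allocation that is already known at enrolment.

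The reply is also right about the size of the slip effect. Under readings (a) and (b) little beyond the tail is exposed. A reader might infer from slips numbered 1 to 3 that the draw works in blocks of three, and so that allocation is 61% predictable. The text does not say that, so 61% is a conditional worst case.

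Three further inferences are tempting and are not supported:
- *Lack of stratification lets in selection bias.* The article names two sites ("The recruitment sites for this research are the departments of neurology, West China Hospital of Sichuan University and department of neurology, Chengdu Second People's Hospital") and describes no stratification, but a condensed article may leave that out. Without it, hospitals can be unbalanced across arms by chance, which is not selection bias.
- *The draw leaves no auditable record.* The section itself refers to a generated sequence, and silence on record-keeping proves nothing here.
- *Allocation is seriously predictable under any form of the draw.* Readings (a) and (b) show otherwise.

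**Conclusion.** The point holds on the roles. As written, generation of the sequence and enrolment belong to the same role, in conflict with the safeguard described earlier in the same section. Coming allocations can therefore be known when a patient is approached, and selection bias can enter. Its size cannot be calculated, since it depends on what the assistants know and do.

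The slip draw is a secondary weakness, and its extent is undetermined: 37%, 39% or 61% correct guesses against 33%, depending on a rule that the text does not give. These figures assume an enroller who tracks the arm counts but has not seen the sequence, recruitment that runs to exactly 183, and, under (a), equal probability among open arms.

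This should be corrected before the first patient is randomised, because concealment cannot be restored afterwards.

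**What to change.** 1. Replace the slip draw, and the sentence giving sequence generation to the enrolling assistants, with a computer-generated 1:1:1 list in permuted blocks. Block sizes should be multiples of three, varied at random and not disclosed to those who enrol.
2. Name, by role, an existing team member to generate and hold the list who neither enrols, intervenes nor assesses. Under Data management and statistical analysis, the coordinating centre also coordinates recruitment and home interventions, so membership of it does not by itself establish independence.
3. Release each assignment, by sequentially numbered opaque envelopes or a central call, only after consent and the baseline (T0) assessment are recorded. Screening and the pre-discharge session both fall on the day before discharge, so this order should be written down.
4. Accept that arms may not end at exactly 61. If the largest block were 9 (three per arm), an unfinished block could leave a gap of at most 3 between arms, or 6 with a separate list for each of two hospitals.
5. Optionally, stratify the list by hospital. This protects against chance imbalance and is not needed to answer the concealment problem.

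The cost is one list, a division of roles among existing staff and a short amendment. The planned total of 183 stays. Trial status says recruitment had not begun at submission; if it has begun since, the change protects only later participants, and the report should state how the earlier ones were allocated.

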### Participants

Patients with stroke who are about to be discharged from departments of neurology in the West China Hospital of Sichuan University and Chengdu Second People's Hospital, will be recruited and followed up until week 24 after randomization. Trained investigators and research assistants will approach and inform patients about the study protocol, the randomization process, and the details of the intervention. Participants will sign an informed consent form prior to participation in the study. The inclusion criteria are as follows: (1) meeting the diagnostic criteria of ischemic stroke, confirmed by brain CT or magnetic resonance imaging; (2) stable condition; (3) muscle strength grade II or above, Barthel Index > 40; (4) age ≥ 18 years old; (5) clear consciousness and ability to communicate with researchers through writing/language; (6) residence in Chengdu; (7) discharge home rather than to other care institutions; (8) ability to use a mobile phone and WeChat; and (9) voluntary participation in the study.

The exclusion criteria are as follows: (1) previous history of mental illness or existing mental disorder and (2) serious concomitant diseases, such as severe hepatic and renal insufficiency, severe arrhythmia, frequent angina pectoris, heart failure, and myocardial infarction.

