### Evaluation methods

An assessor-blind method is used; that is, questionnaire collectors are research assistants who are trained in the use of measurement tools but are blinded to the grouping of study subjects. The intervention effects of the three groups of patients will be measured at baseline and 2 months, 3 months, and 6 months after discharge. The evaluation content includes questionnaire surveys and biochemical index measurements. Baseline data (during hospitalization) collection: Patients will complete the assessment at the nurses’ station. Follow-up data (after discharge from the hospital) will be collected as follows: The research assistant will visit the patient at home for data collection. Patients will complete the assessment independently, but those with reading difficulties, visual impairment, or handwriting difficulties will be instructed to complete the questionnaire as each item is read to them in neutral, noncryptic language. After the evaluation, the researchers will check whether the evaluation is complete. If there are missing items, patients will complete the items on the spot and return the evaluation for verification again. Any doubts about the content will be verified with the patient on the spot. Upon completion of data collection at each follow-up time point, each study patient will receive a gift for participating in the study. Basic demographic data will be collected at baseline, including age, sex, ethnicity, education level, marital status, job status, family status, and medical condition.1. Primary outcome (for patients)

The primary outcomes are neurological function status, self-management behavior, quality of life, biochemical indicators, recurrence rate, and unplanned readmission rate.

Neurological status

The National Institutes of Health Stroke Scale (NIHSS) is the most common stroke evaluation index in the world. It covers the anterior and posterior circulation of the brain, including consciousness, movement, sensation, speech, and visual field, with a total of 15 items. NIHSS scores range from 0 to 42, with higher scores indicating more severe neurological impairment [43]. Cai Yefeng et al. introduced the NIHSS in China to conduct a multicenter and large sample test, and the results showed that the Chinese version of the NIHSS had good reliability, validity, and sensitivity [44].

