### Improving adherence to interventions, modifications, and post-trial care

To improve adherence to interventions in each intervention, we repeatedly emphasized the importance of wearing smartwatches to monitor physical signs for patients’ recovery. And the study required patients to upload self-management logs to the cloud platform every other day. The system will have a built-in reminder module to remind patients through WeChat and mobile phone messages. As a reward, patients who upload their reflection logs on time each week will receive a small gift. This study focuses on health education. The medical treatment or rehabilitation methods of patients in the home stage are based on the doctor’s advice, and the study does not involve additional or alternative medical treatment and rehabilitation methods. If the patient has a need during follow-up, the investigator will communicate with the patient’s doctor to provide the patient with a solution to the problem as an alternative treatment or rehabilitation method. After the intervention, the smartwatch will be taken back, but the WeChat group will not be dissolved. Patients can contact the medical staff in the WeChat group for answers if they have any questions.

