This study has some limitations. First, the study population is focused on patients with ischemic stroke, and the findings may not be generalizable to patients with hemorrhagic stroke. Second, the main purpose of this study is to improve the self-management ability of patients, that is, patients are required to have a certain degree of self-care ability, so the inclusion criteria required that the BI index be greater than 40, which may have limited the participation of some severely ill patients, and these patients also need our attention. Based on the above limitations, we will extend transition management based on wearable devices to hemorrhagic stroke and critically ill patients in future research. In addition to these limitations, the data collected by the wearable devices used in the study may be inaccurate due to the device or the improper way that patients wore the device. To mitigate these risks, research assistants will repeatedly teach patients and informal caregivers about how to wear and use the device during enrollment, emphasizing the precautions, and allowing patients to practice many times until they become proficient. The wearable device used in this project is a medical-grade smartwatch that can measure blood pressure, heart rate, electrocardiogram, sleep, blood oxygen, exercise status, and other functions. It has been registered as a class II medical device by the China Food and Drug Administration and has good stability and accuracy. At present, research on the “real-time support” care model of stroke patients’ self-management could provide new ideas for breaking through the bottleneck of stroke patients’ insufficient self-management ability. The findings of this work will (1) provide evidence-based information on innovative interventions for patients with stroke during the transition period; (2) offer real-time and precise intervention for patients through wearable technology, stepping out of the original thinking of a single intervention plan, giving patients individualized intervention models based on dynamic patient data, and providing empirical evidence for the application of wearable technology in stroke patients; and (3) stimulate patients’ positive mind set and improve their adaptability in the face of adversity based on resilience theory.

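### Patients are declared blinded and all outcomes objective, but the design reveals the arm to patients, two primary outcomes are self-completed, and assessor blinding at home visits is doubtful

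*Protocol article*

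**What the plan says.** Under Randomization and blinding, the protocol article concedes that intervention practitioners cannot be blinded, then states that "patients, data collectors, and statisticians will be blinded to the intervention allocation". It adds, for all outcomes without exception, that "the outcomes of this study will be objectively measured and not influenced by the unblinded intervention". The same section provides that "all participants in the smartwatch intervention group and the wristband group will sign a confidentiality agreement", so that controls do not learn of the study from them.

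Under Evaluation methods it repeats the assessor claim: "questionnaire collectors are research assistants who are trained in the use of measurement tools but are blinded to the grouping of study subjects". Follow-up data are collected by a research assistant at the patient's home 2, 3 and 6 months after discharge, and patients fill in the assessment themselves unless they need items read to them. The primary outcomes include self-management behavior (SSBR), quality of life (SF-12 v2) and neurological function (NIHSS, MBI), alongside glucose and blood pressure, recurrence and unplanned readmission.

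Under Participants, the recruiting staff are to "inform patients about the study protocol, the randomization process, and the details of the intervention".

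**The concern.** Blinding of patients would require that they could not tell which arm they are in. Here one arm gets a smartwatch with about ten coaching contacts in eight weeks, one gets a different wrist device, and one gets routine care with no device or sham described. Patients who have been coached on self-management and then rate their own self-management may report more favourably whether or not their behavior has changed.

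The abstract's stated aim is efficacy on self-management behavior, and the hypothesis names quality of life. Both are measured by self-report. If the two sentences stand, the trial report would claim a protection against reporting bias that these outcomes do not have. The limitations paragraph in the Discussion does not mention the issue.

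**Working it through.** The point rests on comparing sections. The article gives no figure to reproduce.

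**Patients**
- Smartwatch arm: patients are taught to use the watch the day before discharge and then coached (Study interventions).
- Wristband arm: patients wear a different device and monitor themselves, without the RISS program (Study interventions).
- Both device arms sign the confidentiality agreement, which presupposes that they know they are not controls.
- Control arm: routine care only. The Participants section does not limit disclosure of the intervention details by arm, so a control who has heard them and gets no device can infer the allocation.

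Patient blinding is therefore contradicted outright for the two device arms, and not credible for controls.

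**Outcomes**
- SSBR (51 items, total 51 to 255) and SF-12 v2 are self-completed questionnaires. So are patient secondary scales such as PHQ-9 and CD-RISC 10.
- NIHSS and MBI are scored ratings, exposed to what the rater knows.
- Glucose and blood pressure are read from meters. Recurrence and readmission are events.

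The unqualified objectivity sentence can hold at most for the last group.

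**Assessors**
- The intervention lasts 6 months, so the 2- and 3-month visits fall inside it and the 6-month visit falls at its end. The smartwatch is taken back only after the intervention.
- Visits are face to face at home, and no step to hide the device is described.
- Questionnaire collectors are research assistants. Research assistants also generate the sequence and enrol (Randomization and blinding), and the Discussion says "research assistants will repeatedly teach patients and informal caregivers about how to wear and use the device during enrollment". No separation of these roles is stated.

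**Illustration of size**

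The documents give no size for a reporting shift, so 0.1 to 0.3 SD is an assumption.

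Inputs: 53 per arm (Sample size, before the addition for losses); true effect zero; shift b in the smartwatch arm only; three pairwise Bonferroni comparisons (Data management and statistical analysis), so two-sided alpha = 0.05/3 = 0.0167 and z = 2.394.

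SE of a two-arm difference = sqrt(2/53) = 0.194 SD.

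Probability of a significant result favouring the smartwatch = 1 − Φ(z − b/SE):

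| Shift b | b/SE | Bonferroni (z = 2.394) | Unadjusted (z = 1.960) |
|---|---|---|---|
| 0 | 0 | 0.8% | 2.5% |
| 0.1 SD | 0.515 | 3.0% | 7.4% |
| 0.2 SD | 1.030 | 8.6% | 17.6% |
| 0.3 SD | 1.544 | 19.8% | 33.9% |

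This takes each pairwise test on its own, without first requiring a significant ANOVA. For the three-group ANOVA with only the smartwatch mean shifted, f = b × √2/3, and the rejection rate is 7.7%, 16.8% and 33.3% for the three shifts, against a nominal 5%. With all 61 per arm retained the rates are slightly higher: the two-sided Bonferroni figures are 3.4%, 9.9% and 23.1%, against 1.67%.

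**The case against.** Four points can be made for the protocol.

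**Assessors may in fact be blinded.** The article says they are, and a shared job title does not show that the same people fill each role. The randomization section itself mentions a research assistant who does not know the study design, and device teaching is placed at enrolment rather than at follow-up visits. The full protocol may separate the roles. This stands: a reader might infer that the NIHSS rater is unblinded, but the documents do not say so. What remains is that visits at home during device use threaten blinding even with separate staff, and no safeguard is described.

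**Some primary outcomes are largely objective.** This also stands. It argues for limiting the objectivity sentence rather than removing it.

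**The size of the bias is unknown, and the plan adjusts for multiplicity.** Both are true. The Bonferroni figures are therefore the relevant ones, and they are clearly lower than the unadjusted ones. They are still several times the nominal 0.8%.

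**The confidentiality agreement protects controls.** It may reduce what controls learn from device-arm patients. It cannot blind the device arms, and it does not undo what recruiting staff have already explained.

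A reader might also infer that one shared WeChat group gives controls access to staff advice and so dilutes the contrast between arms. The documents do not support this. The Recruitment section mentions a study WeChat group but no staff in it. Staff access appears only in a passage about what follows the intervention ("the WeChat group will not be dissolved. Patients can contact the medical staff in the WeChat group for answers"). Whether groups are separate by arm is a detail the full protocol may settle. No contamination or loss of power is claimed here.

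**Conclusion.** The concern holds in three parts of different strength.

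1. **Patient blinding** is wrong as stated. This rests on the article's own description of the arms.
2. **Universal objectivity of outcomes** is wrong as stated. It fails for SSBR and SF-12, which are self-completed, and is not secured for NIHSS and MBI, which are scored ratings.
3. **Assessor blinding** is doubtful, not disproved. It is a strong inference from home visits during device use and from unseparated roles.

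Blinding of statisticians and data-entry staff is not in question.

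Under an assumed shift of 0.1 to 0.3 SD, 53 per arm and Bonferroni 0.05/3, the false-positive rate in the smartwatch's favour rises from 0.8% to between 3% and 20%. The range illustrates what such a shift would do and does not estimate the bias in this trial. The point should be corrected, but it is not fatal, because several primary outcomes are less exposed.

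**What to change.** 1. State that patients, caregivers and intervention staff are not blinded.
2. Limit the objectivity sentence to meter-measured glucose and blood pressure, recurrence and readmission. Word conclusions on SSBR, SF-12 and the other self-report scales as open-label.
3. From the existing staff, assign the 2-, 3- and 6-month visits to research assistants with no part in allocation, enrolment or device teaching.
4. Ask patients to keep any device out of the assessor's sight during the visit and not to mention it. Have the assessor record a guess of the arm at each visit, so that the report can show how far blinding held.

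The cost is less flexible rostering and a weaker blinding claim. If a device is taken off for the visit rather than only kept from view, there is also a brief gap in the monitoring that feeds the platform's warnings, which the investigators need to weigh. No extra patients or staff are needed, and the only added data item is the assessor's guess.
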